## Abstract

**Background:**

Overweight and obesity among adults are a growing global public health threat and an essential risk factor for various noncommunicable diseases. Although intermittent fasting is a generally new dietary approach to weight management that has been increasingly practiced worldwide, the effectiveness of 2 days per week dry fasting remains unclear.

**Objective:**

The Cardiometabolic and Anthropometric Outcomes of Intermittent Fasting study aims to determine the cardiometabolic, anthropometric, dietary intake, and quality of life changes among civil servants with overweight and obesity, following combined intermittent fasting and healthy plate (IFHP) and healthy plate (HP) and explore the participants’ experiences.

**Methods:**

We designed a mixed methods quasi-experimental study to evaluate the effectiveness of the IFHP and HP methods among adults with overweight and obesity. A total of 177 participants were recruited for this study, of which 91 (51.4%) were allocated to the IFHP group and 86 (48.6%) to the HP group. The intervention comprised 2 phases: supervised (12 weeks) and unsupervised (12 weeks). Data collection was conducted at baseline, after the supervised phase (week 12), and after the unsupervised phase (week 24). Serum and whole blood samples were collected from each participant for analysis. Data on sociodemographic factors, quality of life, physical activity, and dietary intake were also obtained using questionnaires during data collection.

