### Objectives

Although weight loss has been reported in studies of conventional IF, the adaptive phenomenon of dry IF on 2 nonconsecutive days per week on cardiometabolic and anthropometric outcomes remain unclear. Similarly, although the Malaysian Healthy Plate policy has been widely practiced and publicized since 2010, the effectiveness of this eating plan in improving cardiometabolic risks and promoting weight loss is still not well documented. Thus, we established the Cardiometabolic and Anthropometric Outcomes of Intermittent Fasting study to determine the cardiometabolic, anthropometric, dietary intake, and quality of life changes among civil servants with overweight and obesity, following combined IF and healthy plate (IFHP) and healthy plate (HP) and explore the participants’ experiences throughout the study. We hypothesized that combining dry IF and HP diet protocols will improve these parameters more than HP alone.

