## Methods

### Study Design

This is a quasi-experimental study applying a mixed study method that consists of 2 parts: quantitative and qualitative. The quantitative part involved allocating participants into 2 intervention arms: the combined IFHP group and the HP group and measuring the parameters of cardiometabolic risk and anthropometrics at baseline, month 3 and month 6. The qualitative part aimed to explore the facilitators and barriers that enabled or admonished the success of weight loss in the IFHP group through focus group discussions (FGDs) conducted at month 6.

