### Data Analysis

Analysis was conducted using the SPSS software (version 25; IBM Corp). Data for continuous variables were presented as mean (SD) or as median (IQR) for nonnormally distributed data. For categorical variables, frequencies were calculated and are presented as percentages. Variables were compared using the independent 2-tailed *t* test or Mann-Whitney *U* test for continuous variables and the chi-square or Fisher exact (n≤5 in any cell) test for categorical variables. All statistical tests were 2-sided, and the significance level was set at *P*<.05. In further analysis, repeated measures ANOVA will be used to compare the within- and between-group changes in the outcomes, adjusted for possible confounders such as age, ethnicity, and gender.

Data from the FGDs were analyzed using thematic analysis. Interviews transcribed verbatim were independently read by a qualitative researcher ([name]) to identify the preliminary codes. An interpretivist approach was taken to interpret and code participants’ experiences for the entire study. In this way, the coding of participants’ feedback was performed without assumptions or subjective interpretation by the researchers. Meaning units were reviewed, identified, and sorted into codes, before grouping them into categories. Finally, through consensus, the content of each category group was summarized and grouped into main themes. The best representative participants’ quotes for each theme were chosen to support the results. Thematic analysis was used, where initial open codes were generated from the data, after which the codes were organized into larger themes.

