## Discussion

### Principal Findings

We hypothesized that there would be a significant improvement in cardiometabolic and anthropometric parameters among participants in the IFHP group following the intervention after 3 and 6 months. We expected that these changes would also be present among participants in the HP group, but the degree of change would be more prominent among participants in the IFHP group. We also believe that the effectiveness of the intervention in improving cardiometabolic and anthropometric outcomes was driven by both personal motivation and a strong support system.

The preliminary results showed no significant differences in most sociodemographic characteristics and anthropometric measurements of the participants between the 2 intervention groups. The significant difference observed in job categories is most likely because of the departmental units stationed at the Institute for Medical Research Jalan Pahang being diagnostic based; thus, there was a higher proportion of medical laboratory technologists in the HP group than in the IFHP group.

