### Strengths and Limitations

A strength of our study is that we applied both quantitative and qualitative methods. The mixed method allows us to measure the effectiveness of the intervention and explore the challenges of practicing it simultaneously. This integrated framework is crucial for a better understanding of the challenges faced during dietary intervention in obesity prevention programs so that it can be improvised in future programs to improve the outcomes and sustainability of health changes.

The main limitation of our study is the effect of the movement control order due to the COVID-19 pandemic on intervention compliance and weight management. The implementation of movement control orders and work from home for those working would limit their physical activity, expose them to unhealthy eating, reduce their motivation toward weight loss, and affect their control of food intake. Studies have shown that social lockdowns have negative consequences on weight-related behavior and weight management [26,27].

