### Conclusions

With the increase in the prevalence of overweight and obesity worldwide, a weight loss method that is not only effective but also practical and easy to comply with is required. Although IF has been widely practiced and studied, data on the effectiveness of dry fasting in reducing weight and cardiometabolic risk are limited. We established the Cardiometabolic and Anthropometric Outcomes of Intermittent Fasting study to determine the effectiveness of a combined IFHP and HP in improving anthropometric and cardiometabolic outcomes among civil servants with overweight and obesity. The mixed methods study was designed to measure the changes quantitatively, reflect the participants’ points of view, and ensure that the study findings are grounded in their experiences. The study findings and their in-depth explanation may contribute to the development of more effective and feasible obesity prevention methods, improve current health policies, and provide new insights that will stimulate new research questions in the future.

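### With two active arms and no untreated comparator, the study cannot show that HP or IFHP is effective; its aim and inference should rest on the IFHP v HP difference in change

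*Protocol article*

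**What the plan says.** The abstract's Methods paragraph gives the purpose as "to evaluate the effectiveness of the IFHP and HP methods among adults with overweight and obesity". The abstract's Conclusions repeat this in similar terms, and the closing Conclusions section says the study was set up "to determine the effectiveness of a combined IFHP and HP in improving anthropometric and cardiometabolic outcomes". The Objectives section remarks of HP that "the effectiveness of this eating plan in improving cardiometabolic risks and promoting weight loss is still not well documented" and presents the study as the response.

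On design, Study Design says "The quantitative part involved allocating participants into 2 intervention arms: the combined IFHP group and the HP group". No untreated, waiting-list or usual-diet group appears anywhere in the article.

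On analysis, Data Analysis says "repeated measures ANOVA will be used to compare the within- and between-group changes in the outcomes". Principal Findings adds the hypothesis that "there would be a significant improvement in cardiometabolic and anthropometric parameters among participants in the IFHP group following the intervention", and expects such changes in the HP arm too, though to a lesser degree.

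Alongside this runs a comparative strand. The Objectives section states: "We hypothesized that combining dry IF and HP diet protocols will improve these parameters more than HP alone". The Sample Size section follows rules for a two-group comparison.

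**The concern.** An aim of establishing that a diet is effective needs a comparison with what would have happened without it. For HP, the article offers only change from baseline. For IFHP, it offers change from baseline and a comparison with another active diet. If a fall in weight or glucose within the HP arm were read as evidence that HP works, the design could not support that reading. The error can also run the other way: a flat HP arm could conceal a real benefit offset by the restrictions in force during the study. HP is a national dietary policy tool whose effect the article says is poorly documented, so this is a conclusion readers would look for.

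**Working it through.** **1. What each comparison identifies.** Let D_I and D_H be the effects of IFHP and HP against no intervention, and B_I and B_H the changes that would have occurred in each arm anyway.

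- Change within HP = D_H + B_H.
- Change within IFHP = D_I + B_I.
- Difference in change = (D_I − D_H) + (B_I − B_H).

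Nothing in the study measures B_H or B_I, so neither D_H nor D_I can be separated out. The difference in change removes the background only if B_I = B_H.

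**2. Why B is unlikely to be zero, from the article itself.**

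- Recruitment Phase: only volunteers judged ready by interview were enrolled, and each signed a behavioral contract.
- Study Participants: 28 + 27 = 55 withdrew, and 55/177 = 31%. Of these, 24 of 55 could not commit to the intervention. Completers were 91 − 28 = 63 (IFHP) and 86 − 27 = 59 (HP).
- Strengths and Limitations: the movement control order "would limit their physical activity, expose them to unhealthy eating, reduce their motivation toward weight loss".
- Passage of time over 6 months.

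**3. What the study was sized for.** With a difference of 5%, SD 10%, two-sided α = 0.05 and power 0.80 (Sample Size; Data Analysis for sidedness), the normal formula gives n per arm = 2 × (1.960 + 0.842)² × (10/5)² = 62.8, so 63. The two-sample t-test gives 63.8, so 64. The stated 64 is reproduced as the number per arm for IFHP v HP. The sample size therefore belongs to the comparative question, not to an effect of HP on its own.

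**4. Illustration of a within-arm test when the diet has no effect.** Suppose D = 0 and weight shifts by b% for other reasons. The one-sample t-test has noncentrality b√n/SD. For b = 2, SD = 10 and n = 63 this is 0.2 × 7.94 = 1.59, and the test is significant in 35% of trials. The shifts b are assumptions. The SD of 10% is the article's figure, assumed to apply to change; the SD of 5% is an assumption.

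| Assumed shift | SD 10%: n = 63 / 59 | SD 5%: n = 63 / 59 |
|---|---|---|
| 0% | 5% / 5% | 5% / 5% |
| 1% | 12% / 12% | 35% / 33% |
| 2% | 35% / 33% | 88% / 86% |
| 3% | 65% / 62% | over 99% / over 99% |

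A shift of 1 to 2 percentage points would be 1/5 = 20% to 2/5 = 40% of the 5% target, and it enters each within-arm estimate in full.

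**The case against.** The strongest reply is that the comparative framework is already there: the hypothesis is that IFHP does better than HP, the sample size is for two groups, and the planned ANOVA includes between-group change. The full objective speaks of determining changes after each diet, which can be read descriptively. This stands, and it is why the remedy is small. It does not remove the effectiveness aim stated in the abstract and the Conclusions, nor the rationale about HP in the Objectives section. An unseen analysis plan could not supply the missing comparator either.

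Several stronger readings are tempting, but the article does not support them.

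- A reader might infer that HP's effectiveness is to be proved by a within-group test. No sentence ties the two together; the article plans within-group comparisons and separately states an effectiveness aim.
- A reader might infer that significance in one arm will be set against significance in the other. Principal Findings goes on to expect a larger change in IFHP, and a between-group comparison is planned.
- A reader might infer that unsuccessful participants dropped out. The listed reasons are pregnancy, inability to commit, transfer, new diagnoses on medication and other; weight results of those who left are not given. Selective withdrawal is possible but not shown.
- A reader might infer that restrictions are reported to have altered participants' behavior. The article says they would do so, and reports no observed change.
- A reader might infer that IFHP v HP is a clean causal estimate. Study Site says arms were assigned by institute, and ethnicity (P=.02) and job category (P<.001) differ at baseline in Table 2.

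**Conclusion.** The point holds as one about what may be concluded. With two active arms, neither HP nor IFHP can be shown effective against no intervention, and the within-group part of the analysis cannot fill that gap. The bias in a within-arm change equals the unmeasured background change; its size and direction cannot be estimated from this study. The table above shows only how readily a modest background shift yields a significant result, and it rests on assumed shifts and assumed SDs of change. The estimable quantity is the IFHP v HP difference in change. It is a non-randomised contrast in which arm and institute coincide, so it is free of background change only if that change was common to the institutes. The article does not itself claim that HP has been shown to work; the fault lies in an aim that invites the claim.

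**What to change.** - Restate the objective and both sets of conclusions as the difference between IFHP and HP in change from baseline. This agrees with the stated hypothesis and sample size.
- Base inference on the group-by-time contrast at month 3 and at month 6.
- State with that contrast that allocation was by institute and that ethnicity and job category differed at baseline. Age, ethnicity and gender are the adjustment examples named; job category is not among them. Adjustment for individual characteristics cannot fully separate arm from institute.
- Report within-arm changes with confidence intervals as descriptive only, without significance claims and without stating that either diet is effective against no intervention.

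The article describes the repeated measures analysis in the future tense, so this can still be done without new data. The cost is rewording and the loss of one headline claim. Keeping the aim of showing that HP itself works would need an untreated or usual-diet comparison group, which this study does not have.

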**Results:**

Most of the participants were female (147/177, 83.1%) and Malay (141/177, 79.7%). The expected outcomes of this study are changes in body weight, body composition, quality of life, physical activity, dietary intake, and cardiometabolic parameters such as fasting blood glucose, 2-hour postprandial blood glucose, hemoglobin A1c, fasting insulin, and lipid profile.

**Conclusions:**

The Cardiometabolic and Anthropometric Outcomes of Intermittent Fasting study is a mixed methods study to evaluate the effectiveness of combined IFHP and HP interventions on cardiometabolic and anthropometric parameters and explore participants’ experiences throughout the study.

**Trial Registration:**

ClinicalTrials.gov NCT05034653; https://clinicaltrials.gov/ct2/show/NCT05034653

**International Registered Report Identifier (IRRID):**

RR1-10.2196/33801

## Introduction

### Background

The overweight and obesity epidemic has become one of the most alarming public health threats. Although largely preventable, the worldwide prevalence of obesity nearly tripled between 1975 and 2016 and shows an increasing trend. In 2016, >1.9 billion adults were overweight, and 650 million were obese. If this current trend continues, it is estimated that 2.7 billion and >1 billion adults will be overweight and obese, respectively, by 2025 [1]. In Malaysia, the National Health and Morbidity Survey (NHMS) 2019 reported that 50.1% of adults were either overweight (30.4%) or obese (19.7%), which increased compared with the NHMS 2011 (overweight 29.4% and obesity 15.1%) and 2015 (overweight 30% and obesity 17.7%) findings [2].

The relationship between obesity and poor health outcomes is well established. Despite the increased risk of noncommunicable diseases such as hypertension, diabetes, stroke, coronary heart disease, and certain cancers, a growing body of literature has demonstrated a positive relationship between obesity and various mental health issues such as depression and poor quality of life [3,4]. The World Health Organization has established multiple strategies that describe the actions that need to be taken by stakeholders at the global, regional, and local levels to combat obesity in adults and children. Furthermore, effective and feasible policy actions have been included in the “Global action plan on physical activity 2018-2030: more active people for a healthier world” to increase physical activity globally [1].

As obesity occurs because of a positive energy balance in the body, strategies for preventing and treating obesity mainly focus on dietary modification and increasing physical activity. A form of calorie restriction dietary protocol is intermittent fasting (IF), which encompasses various eating diet plans that cycle between fasting and nonfasting states over a defined period to create a negative energy balance, thereby inducing weight loss. Studies have shown that IF is effective in reducing body weight and improving metabolic outcomes [5,6]. Although the effects of wet IF have been well documented, the benefits of dry IF (except for Ramadhan fasting for Muslims) have not been clearly indicated in previous studies. Wet or water IF is defined as fasting during which all food and drink except water are restricted [7], whereas dry IF is complete fasting without any food and fluid intake [8]. In countries with predominantly Muslims, the practice of dry fasting during Ramadan and the voluntary 2 days per week fasting (Mondays and Thursdays) are widely conducted.

As portion size is a crucial determinant of energy intake, portion control by controlling serving size is another practical method for reducing calorie intake and promoting weight loss. This portion-control method has been widely practiced and studied worldwide, using different portion divisions depending on the culture and eating habits [9,10]. The Malaysia Healthy Plate, a portion-control dietary plan, was created to translate the messages in the Malaysia Dietary Guideline 2010 and Malaysia Food Pyramid 2010 [11]. It is a visual tool that emphasizes the quarter-quarter-half concept and provides a quick visual technique that helps ensure that the intake of food is within the recommended guidelines. Specifically, the Malaysia Healthy Plate is a single-meal guide that divides the plate into a quarter plate of grains or grain products; a quarter plate of fish, poultry, meat, or egg; and a half plate of fruits and vegetables [12].

### Objectives

Although weight loss has been reported in studies of conventional IF, the adaptive phenomenon of dry IF on 2 nonconsecutive days per week on cardiometabolic and anthropometric outcomes remain unclear. Similarly, although the Malaysian Healthy Plate policy has been widely practiced and publicized since 2010, the effectiveness of this eating plan in improving cardiometabolic risks and promoting weight loss is still not well documented. Thus, we established the Cardiometabolic and Anthropometric Outcomes of Intermittent Fasting study to determine the cardiometabolic, anthropometric, dietary intake, and quality of life changes among civil servants with overweight and obesity, following combined IF and healthy plate (IFHP) and healthy plate (HP) and explore the participants’ experiences throughout the study. We hypothesized that combining dry IF and HP diet protocols will improve these parameters more than HP alone.

## Methods

### Study Design

This is a quasi-experimental study applying a mixed study method that consists of 2 parts: quantitative and qualitative. The quantitative part involved allocating participants into 2 intervention arms: the combined IFHP group and the HP group and measuring the parameters of cardiometabolic risk and anthropometrics at baseline, month 3 and month 6. The qualitative part aimed to explore the facilitators and barriers that enabled or admonished the success of weight loss in the IFHP group through focus group discussions (FGDs) conducted at month 6.

### Study Site

The participants were allocated to each intervention arm according to the institutes in the National Institutes of Health in Setia Alam; the Institute for Medical Research, Jalan Pahang; and the Institut Latihan Kementerian Kesihatan Malaysia (Teknologi Makmal Perubatan), Jalan Pahang. The distance between Jalan Pahang and Setia Alam is approximately 40 km. The allocation was done in such a manner to avoid contamination bias. The study population had a relatively similar sociodemographic features, environment, facility, and nature of work. The allocation of the intervention was determined a priori and was based on the feasibility of monitoring the study participants.

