#### Sample Size

Sample size calculation was conducted using a power and sample size program. It followed the rules required for comparison between the 2 groups [13]. The sample size was estimated using the level of significance (α=.05) and power of the study (1-β=.80), minimum suggested difference (delta) of 5% (SD 10%) weight loss that may be achieved under this intervention, and the corresponding differences among groups. The assumption of 5% weight loss used in the sample size calculation was based on a review conducted by Ryan and Yockey [14], which stated that a minimum weight loss of 5% is needed to improve cardiometabolic risk such as hypertension, diabetes mellitus, and hyperlipidemia. The minimum sample size required for this study was 64 participants. Considering 40% attrition, the required sample size for each arm was 90 participants. A total of 180 participants were required for this study.

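### Arms were assigned by institute, and probably coincide with campus, so the stated 5% error rate and 80% power hold only if institute or campus has no effect on change.

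*Protocol article*

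**What the plan says.** **Allocation.** Study Site states: "The participants were allocated to each intervention arm according to the institutes in the National Institutes of Health in Setia Alam", followed by two institutes at Jalan Pahang. It adds "The distance between Jalan Pahang and Setia Alam is approximately 40 km" and "The allocation of the intervention was determined a priori and was based on the feasibility of monitoring the study participants". The stated reason for using institutes is to avoid contamination. The same section asserts: "The study population had a relatively similar sociodemographic features, environment, facility, and nature of work".

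**Sample size.** The Sample Size section says of the calculation: "It followed the rules required for comparison between the 2 groups". It uses α=.05, power .80, a difference of 5% and an SD of 10%. This gives 64, then 90 per arm after 40% attrition. No ICC or design effect is mentioned.

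**Analysis.** Data Analysis names individual-level t, Mann-Whitney, chi-square and Fisher tests. Repeated measures ANOVA will follow, adjusted for confounders of which age, ethnicity and gender are given as examples. Institute and job category are not named.

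**Baseline.** Table 2 reports job category P<.001 and ethnicity P=.02. Principal Findings explains the surplus of laboratory technologists in the HP arm by "the departmental units stationed at the Institute for Medical Research Jalan Pahang being diagnostic based".

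**Limitations.** Strengths and Limitations says: "The main limitation of our study is the effect of the movement control order due to the COVID-19 pandemic". Allocation by institute is not listed.

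**The concern.** When whole institutes are assigned, people in one workplace may change alike for reasons unrelated to the diet. A calculation that treats them as independent leaves this shared variation out of the standard error. If each arm also sits on one campus, a campus difference in weight change cannot be told apart from an intervention difference.

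The main claim is at stake. The Objectives hypothesise that IFHP improves outcomes more than HP alone, and that comparison is between sites. The assurance that the populations are alike, which would make the condition easier to accept, is partly contradicted by the article's own baseline table.

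**Working it through.** **1. The plan's own figure.** Inputs from Sample Size and Data Analysis: difference 5, SD 10 (standardised 0.5), two-sided α 0.05, power 0.80, equal arms. The two-sample t-test formula gives 63.8, so 64 per arm, as stated. Then 64 × 1.4 = 89.6, so 90 per arm, also as stated. Neither step contains an allowance for clustering.

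**2. Which arm was where.** Study Site does not say which institute received which arm. Principal Findings attributes the HP arm's technologists to Jalan Pahang. With the contamination rationale, the natural reading is HP at Jalan Pahang and IFHP at Setia Alam. This is an inference.

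**3. Variance with one campus per arm.** Completers are 63 (IFHP) and 59 (HP), from Study Participants. In units of SD²:

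- Independence: V₀ = 1/63 + 1/59 = 0.0328, a standard error of 10 × √0.0328 = 1.81 percentage points.
- Shared campus effect: V₁ = 2·ICC + (1 − ICC)·V₀.
- Design effect: DE = V₁/V₀, which is close to 1 + 60·ICC with about 61 completers per arm.

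The ICC refers to weight change. It is not in the documents, so it is varied.

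**4. The planned, uncorrected test.** Its statistic has mean λ = 0.5/√0.0328 = 2.76 under the planned effect and 0 under no effect, with variance DE in place of 1. Hence

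- type I error = 2·[1 − Φ(1.96/√DE)];
- power = Φ((2.76 − 1.96)/√DE) + Φ((−2.76 − 1.96)/√DE).

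**5. A design-effect-corrected test.** This assumes a known ICC. Power is t-test power at d = 0.5 with 63/DE and 59/DE people.

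| Assumed ICC | DE | √DE | Type I error, uncorrected | Power, uncorrected | Power, corrected |
|---|---|---|---|---|---|
| 0 | 1.00 | 1.00 | 5% | 79% | 78% |
| 0.01 | 1.60 | 1.26 | 12% | 74% | 58% |
| 0.02 | 2.20 | 1.48 | 19% | 71% | 45% |
| 0.05 | 4.00 | 2.00 | 33% | 66% | 27% |

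At ICC 0 the two power figures differ only because one uses the normal and the other the t distribution.

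**6. If institutes are the clusters.** The number per arm is not stated. Assume 2 to 5 of equal size, with no shared campus effect: DE = 1 + (61/k − 1)·ICC.

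- k = 5, ICC 0.01: DE = 1 + 11.2 × 0.01 = 1.11, type I error 6.3%.
- k = 2, ICC 0.05: DE = 1 + 29.5 × 0.05 = 2.48, type I error 21%.

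**7. Without an ICC.** Suppose weight change differs between campuses by a fixed 1, 2 or 3 percentage points for reasons other than diet. With a standard error of 1.81 and no intervention effect, the planned test rejects 9%, 20% or 38% of the time.

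**8. The similarity statement against Table 2.** IFHP against HP: medical laboratory technologists 17.6% and 39.5%, clerks 25.3% and 3.5%, Malay 87.9% and 70.9%. The claim about nature of work does not fit the job figures. Sex, age, education, income and smoking show no significant difference.

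**The case against.** The design is disclosed. The article calls the study quasi-experimental, gives the unit of allocation and its reason, and reports and explains the job imbalance. The covariate list is open-ended and the article is condensed, so further adjustment may be specified elsewhere. Ethnicity, one of the two imbalances, is already named. Analysing change removes stable level differences between campuses.

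Most of this stands, but it does not remove the point. Disclosing non-randomisation does not justify an independence assumption in the power and P values. Change scores do not remove differences in trend. If arm and campus coincide, no person-level covariate list separates them.

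Several stronger readings are tempting but not supported:

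- *The P values are certainly too small.* That depends on an ICC the documents do not give. At ICC 0 there is no inflation.
- *The planned test has 58%, 45% or 27% power.* Those figures belong to a corrected test with a known ICC. The uncorrected test has about 74%, 71% or 66%. Its fault is mainly an inflated type I error.
- *One campus per arm is a stated fact.* It is inferred from the Discussion.
- *Canteens, local staff or local movement restrictions differed by campus.* The article does not say so, and it describes the movement control order without any site difference.
- *The similarity sentence is wholly wrong.* Most compared baseline characteristics in Tables 2 and 3 did not differ significantly.

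**Conclusion.** The point holds in conditional form. The protocol assigns arms by institute and sizes and tests the comparison as if participants were independent. Its 5% error rate and 80% power are therefore valid only if institute or campus has no effect on change. For the 63 and 59 completers, assuming one campus per arm and an ICC of 0.01 to 0.05, the type I error of the planned test would be about 12% to 33%. The effect is smaller with several institutes per arm and absent at ICC 0.

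Two parts rest on no assumed figure: the similarity claim for nature of work is contradicted by the job-category result, which the article itself attributes to the site, and allocation by institute is missing from the limitations. It is worth correcting because it bears on the main between-arm claim and the outcome analysis is still described as future.

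**What to change.** 1. State that the power and P values are conditional on no institute or campus effect. Report the main contrast also with its standard error multiplied by √DE over an assumed ICC range of 0.01 to 0.05. For the completers with one campus per arm, the multipliers are about 1.26 to 2.00.
2. Add job category to the adjustment set. Where an arm holds more than one institute, use institute as the cluster with a small-sample correction. Say that this captures only clustering within a campus and cannot separate campus from diet.
3. Qualify, rather than delete, the similarity sentence in Study Site for job category and ethnicity. State which institutes received which arm.
4. Name allocation by institute as a main limitation, and word the conclusion as a non-randomised comparison of sites.

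No new data collection is needed. The cost is wider intervals and a more cautious conclusion.
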